### Recruitment {15}

This study will utilize two sites: one in Houston, TX (UTHealth) and one in Los Angeles, CA (UCLA). The UTHealth’s primary recruitment center for veteran and non-veteran population will be the UTHealth Trauma and Recovery Center (TRC). UCLA Department of Psychiatry and Biobehavioral Sciences will be the primary research site in California and will collaborate with the West Los Angeles VA Medical Center to recruit the veteran population. Both sites will additionally utilize contracts with the BuildClinical social media platform to enhance enrollment.

## Assignment of interventions: allocation

### Sequence generation {16a}

Participants will be randomized in a 1:1 ratio to suvorexant or matched placebo using a covariate adjusted randomization algorithm, stratifying allocation by site, sex, and level of sleep disturbance via the ISI score. This algorithm is implemented within REDCap and is run once study coordinators ensure participant signs the informed consent, is eligible for the study, and enters all stratification variables.

### Concealment mechanism {16b}

Once a participant is randomized, the REDCap system will send an automatic email to each site’s pharmacy that includes the participant’s randomized treatment group. Each institution’s pharmacy will be responsible for labeling the unopened prefilled bottles according to the randomization information from the REDCap email. Unique labels for each masked dosing condition will be locked in the study pharmacy in a log/administration book and backed up on the respective university’s secure server.

### Implementation {16c}

The study pharmacist labels prefilled bottles of suvorexant and placebo with an appropriate KIT ID. Only the pharmacist knows which KIT IDs align with the active medication or placebo (the pharmacist will keep a log of this link file in a locked location). Once a participant is randomized, a research staff will pick up the appropriate KIT ID from the pharmacy and dispense it to the participant. The research coordinator will then fill out a Dispensing Case Report Form (CRF) documenting which KIT ID was provided to the participant.

## Assignment of interventions: blinding

### Who will be blinded {17a}

The study will be conducted in a double-blinded fashion in that both the participants and the site investigators and staff interacting with participants and assessing study outcomes will be blinded to treatment assignment.

### Procedure for unblinding if needed {17b}

The pharmacy will maintain the masking record which can be broken only upon request by the study investigators. If the blind is ever broken on any individual participant, the pharmacist will record that fact in the pharmacy dose record.

In instances where the study mask needs to be broken, permission and approval to break the mask will be obtained in advance from appropriate PASA Leadership if possible and does not impact the safety of the participant. Unblinded treatment assignment will come from the local site study pharmacist. Any breaking of the blind will be reported as a protocol deviation.

## Data collection and management

### Plans for assessment and collection of outcomes {18a}

Procedures and assessments specific to the study include medical, cognitive, and motor assessments, clinician-administered assessments, self-assessments, and alcohol cue reactivity.

#### Medical procedures and/or assessments

Breathalyzer: Breathalyzer tests are used to measure participants’ breath alcohol concentration (BrAC). Samples >0.01 g/dl are considered positive. Results are kept in research records and not entered in medical records.Ethylglucuronide (EtG) testing: Ethylglucuronide is a byproduct of ethanol (alcohol that one drinks) and glucuronide, a common biological compound made in the liver that binds various toxins and drugs in the body that allows them to be excreted in the urine. When someone drinks even relatively small amounts of alcohol, EtG is formed and can be detected in the urine.Demographics: The interviewer asks the respondent for his/her date of birth, race, if he or she considers himself or herself to be Hispanic or Latino, and highest-grade level or degree received at the time of the interview.Medical history: This measure is a broad screening tool to collect information on a participants’ medical history, including recent hospitalizations, and check for conditions such as diabetes, liver disease, and kidney disease. It is comprised questions to cover the following areas: allergies, asthma, head, ears, eyes, nose, throat (HEENT), cardiovascular, renal, hepatic, pulmonary, gastrointestinal, musculoskeletal, neurologic, psychiatric, dermatologic, metabolic, hematologic, endocrine, genitourinary, reproductive system, seizure, infectious disease, inflammatory or auto-immune disorders, and diabetes. Screening will include questions to ensure patients are not currently taking any CPY3a inhibitors.Physical examination (PE): A targeted PE will include assessments of the head, eyes, ears, nose, throat, skin, thyroid, neurological system, lungs, cardiovascular system, abdomen (liver and spleen), lymph nodes, and extremities. Height and weight measurements will be taken during screening.Electrocardiogram (ECG): 12-lead ECGs will be obtained using a machine that automatically calculates heart rate and determines intervals for PR, QRS, QT/QTc, and PRT axes.Colombia Suicide Severity Rating Scale (C-SSRS): is a short questionnaire that screens for individuals at risk for suicide.Adverse events: All AEs occurring during the clinical trial will be collected, documented, and reported by the principal investigator/designated study staff according to the specific procedures detailed in section 22 below. Additionally, study staff will assess patients for any medical or psychiatric side effects by asking the participant “How have you been feeling since I saw you last?” and in a manner consistent with Systematic Assessment for Treatment of Emergent Events (SAFTEE) guidelines [25]. Study staff will also review the previous Adverse Event Form and inquire whether any of those events are continuing. Each new or unresolved adverse event will be recorded on the Adverse Event Case Report Form using a brief verbatim term, a severity ranking, and any additional description, according to the procedures. If an adverse event is reported that requires medical attention, it will be reported to a study clinician immediately for review. The PI/trained staff member will review each AE to assess their possible relationship to study medications and expectedness.Prior/concomitant medications (con-meds): Concomitant medications (con-meds) are other prescription medications, over the counter (OTC) drugs, or dietary supplements that a study participant takes in addition to the drug under investigation. Participants are asked to bring all their current medications with them at the time of their screening appointment.Actigraph: This wearable device will be used to measure the SLO and WASO variables in detecting activity and sleep patterns of participants. Participants will be given this device upon successful screening into the study.

#### Clinician-administered assessments

Clinician-Administered PTSD Scale for DSM-5 (CAPS-5): Gold-standard in PTSD assessment. The CAPS-5 is a 30-item structured interview that can be used to make current (past month) diagnosis of PTSD, make lifetime diagnosis of PTSD, and assess PTSD symptoms over the past week [26–28].Clinical Institute Withdrawal Assessment Alcohol Scale Revised (CIWA-AR): This is a common instrument to assess and diagnose the severity of alcohol withdrawal, measuring 10 symptoms via a scale. This instrument takes about 2 min to complete and then scored by a medical professional. Cumulative scores of less than 8–10 indicate mild withdrawal. Next, scores of 8–15 indicate moderate withdrawal, and scores of 15 or more than 15 indicate severe withdrawal with impending possible delirium tremens.Mini-International Neuropsychiatric Interview for DSM-5: Assessment used to determine psychiatric diagnoses. This brief interview is structured and assesses DSM-5 current and lifetime psychiatric diagnoses. Note: Sections B, L, M, and MB will be omitted as these do not impact study inclusion/exclusion [29].Time-Line Follow-Back Assessment Method (TLFB): Interview technique that will be used to obtain quantity/frequency of alcohol consumption data for each day during the 30-day period prior to the study, throughout the period of study participation (measuring drinking on days outside of test session days) and the follow-up. Participants are given a blank calendar covering the time interval to be reconstructed and are asked to reconstruct retrospectively their drinking behavior over that interval. The process is facilitated by establishing anchor points (e.g., holidays, anniversaries, major national events). It can be scored to provide the number of days on which various levels of consumption occurred. The time-line method has good test-retest reliability and good validity for verifiable events. It has been used in numerous studies to compare pre- to post-treatment drinking [30].

#### Self-assessments

PCL-5: The PCL-5 is a 20-item self-report measure that assesses DSM-5-based criteria for PTSD symptoms. Each item is rated on a 5-point Likert-type scale (0 = not at all; 4 = extremely) that indicates how much the participant has been bothered by an identified “worst” stressful event in the past month [31].Insomnia Severity Index Score (ISI): This is a brief questionnaire to screen for insomnia in participants. A scoring system is used to identify what degree insomnia (if any detected) is affecting daily life and sleep patterns.Patient-Reported Outcomes Measurement Information System (PROMIS): This system provides clinicians and study research staff measures of mental and physical health and overall well-being from a patient perspective.Daily diary assessment: Participants will complete daily diary assessments reporting on their mood, alcohol and cigarette craving, motivation to change, self-efficacy, pain, and drinking behavior from the previous day. Participants will complete the DDA electronically during the practice quit attempt (days 0–14). Research staff will distribute the link to the online daily diary assessment during each in-person and virtual visit.

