### Trial design {8}

This is a randomized, double-masked, placebo-controlled study to evaluate preliminary efficacy and safety of SUV (20 mg) for sleep disturbance in AUD and co-occurring PTSD symptoms in approximately 76 randomized men and women veterans and non-veterans between the ages 21 and 65. Following a 7-day placebo run-in, participants will be randomly assigned to receive SUV (10 mg (days 0–6) and 20 mg (days 7–13)) or matched placebo. Participants will be stratified on site, sex, and level of sleep disturbance (Insomnia Severity Index (ISI) score). Post-randomization, all participants will complete an alcohol cue-reactivity paradigm prior to the initial dose of study medication. The alcohol cue-reactivity paradigm is an established laboratory assessment of craving during which participants are exposed to real alcohol and water cues in a bar laboratory setting. Participants will then take their first dose of medication. Participants will begin the real-world practice quit attempt, during which they will attempt to stop drinking for 2 weeks. Participants will complete daily virtual diaries and visits to assess sleep, past-day drinking, and alcohol craving. Participants will return to one of the clinical sites on study day 14 to complete an alcohol cue-reactivity session, to assess post-medication craving. PTSD symptoms will be assessed via Clinician-Administered PTSD Scale for Diagnostic and Statistical Manual of Mental Disorders, Fifth Edition (DSM-5) (CAPS-5) and PTSD Checklist for DSM-5 (PCL-5) at baseline, at day 7, and at day 14 of treatment with SUV or matched placebo.

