### Intervention description {11a}

The study will utilize 10 mg and 20 mg SUV tablets and matching placebo obtained from Merck & Co., Inc., Rahway, NJ, USA. One SUV tablet (10 mg/20 mg) or placebo tablet will be taken orally once daily 30 min before bed with at least 7 h remaining prior to planned awakening. Each participant will be given a placebo run-in (day −7 to day −1). On day −2, participants will be prompted to initiate a 48-h abstinence period. If the study team determines appropriate quit attempts were successful on (verified by self-report + BrAC + EtG) baseline (day 0), the participant will be randomized to SUV or placebo and administered 10 mg SUV or placebo capsules for an additional 7 days (day 0 to day 6). On day 7, the participant previously randomized to SUV will be given 20 mg SUV, and the participant previously randomized to placebo will continue with placebo. The participant will be administered the remaining number of capsules (days 7–13).

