### Outcomes {12}

The primary outcome is change in Insomnia Severity Index (ISI) score, measured as change from baseline to day 14.

Secondary outcomes include change in alcohol craving score from baseline to days 7 and 14, percent of total days abstinent during the 14-day practice quit attempt, mean number of drinks per drinking day as measured by the Timeline Follow Back, and change in PTSD symptoms as measured by change from baseline to days 7 and 14 in the CAPS-5 and PCL-5 score(s).

Exploratory outcomes include actigraphy sleep metrics for sleep latency onset (SLO), wake after sleep onset (WASO), and total sleep duration, as well as the change in PROMIS Sleep Disturbance *T*-score from baseline to day 14.

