A mixed linear model for repeated measures will be used to estimate treatment differences for the change AUQ, PCL-5, and CAPS-5 scores from baseline to days 7 and 14. The model(s) will have fixed effects for treatment, time interval (as a categorical variable), treatment-by-time interaction, and the stratification effects of site, sex, and baseline ISI score. The baseline score for each outcome measure will also be included as a term in the model, as appropriate.

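### The PCL-5 is described with past-month recall but tested as change to days 7 and 14, so half or more of each recalled window precedes the first dose and the estimated PCL-5 difference is pulled toward zero

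*Protocol article*

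**What the plan says.** The Self-assessments section of the Protocol article describes the PCL-5 as 20 self-rated items on how much the participant was bothered by a "stressful event in the past month". It is the only statement of a recall period for this scale in the article.

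The scale has two uses. At screening, a PCL-5 score above 30 is an inclusion criterion (Eligibility criteria {10}). After that it is an outcome: Trial design {8} schedules PTSD assessment with the CAPS-5 and PCL-5 "at baseline, at day 7, and at day 14 of treatment with SUV or matched placebo", and Outcomes {12} lists change to days 7 and 14 as secondary. Statistical methods {20a} estimates "treatment differences for the change AUQ, PCL-5, and CAPS-5 scores from baseline to days 7 and 14" with a repeated-measures model, and places the PCL-5 among five secondary measures under a Benjamini-Hochberg correction.

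Randomised treatment is "SUV (10 mg (days 0–6) and 20 mg (days 7–13)) or matched placebo". It follows a 7-day open-label placebo lead-in.

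For the CAPS-5, the Clinician-administered assessments section gives a past-month use for current diagnosis and says the interview can also "assess PTSD symptoms over the past week".

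**The concern.** A score that looks back a month cannot isolate 7 or 14 days of treatment. Part of what is reported at each follow-up visit took place before randomisation, when the arms cannot differ through treatment. Successive windows also share many of the same days, so part of the change score compares a period with itself.

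This matters because of what the secondary outcomes are for. The Discussion says the outcomes other than the ISI should be taken as generating effect sizes, and expects significant primary or secondary results to support a larger trial. A PCL-5 estimate that is too small for reasons of recall would mislead a decision on PTSD, or the sizing of the next study. No analysis can repair this afterwards, because the recall instruction is fixed when the participant answers.

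**Working it through.** The article states no power or effect figure for the PCL-5, so there is none to reproduce. The check is on the recall windows.

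**Inputs**
- Recall window m: one month (Self-assessments). No day count is given, so 30 days is assumed and 28 to 31 is shown as the range.
- Treated days before the day-7 visit: 7 (days 0-6). Before the day-14 visit: 14 (days 0-13), of which 7 at 20 mg (Trial design {8}, Intervention description {11a}).

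**Share of the window before the first dose** = 1 − (treated days ÷ m)

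| Visit | m = 28 | m = 30 | m = 31 |
|---|---|---|---|
| Day 7 | 1 − 7/28 = 75% | 1 − 7/30 = 77% | 1 − 7/31 = 77% |
| Day 14 | 1 − 14/28 = 50% | 1 − 14/30 = 53% | 1 − 14/31 = 55% |

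**Overlap, m = 30.** The baseline window is days −30 to −1, the day-7 window is days −23 to 6, and the day-14 window is days −16 to 13. Baseline shares 30 − 7 = 23 days with day 7 and 30 − 14 = 16 days with day 14. Days 7 and 14 share 23 days.

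**Dose named in the objectives.** Only 7 of 30 days (23%) in the day-14 window fall in the 20 mg week. The range is 7/31 = 23% to 7/28 = 25%.

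**Direction.** Let W be the total weight that respondents give to days after the first dose. Randomisation makes the expected difference between arms zero on earlier days. The expected difference in the score is therefore W × (weighted mean difference over treated days). If any earlier day receives weight, W is below 1 and the difference moves toward zero. If treatment has no effect, the expected difference is zero for every W, so type I error is not inflated.

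**Why no size is given.** W is unknown. Equal weight on 30 days gives W = 14/30 = 47% at day 14 and 7/30 = 23% at day 7. Weights that halve every 7 days (an assumption for illustration) give (1 − 0.5^(14/7)) ÷ (1 − 0.5^(30/7)) = 0.75/0.949 = 79% at day 14 and 0.50/0.949 = 53% at day 7. The documents do not favour either.

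**With past-week recall.** The windows are days −7 to −1, 0 to 6 and 7 to 13. None overlap, no recalled day at day 7 or day 14 precedes the first dose, and the day-14 window is the 20 mg week.

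**The case against.** The strongest reply is that the Self-assessments entry is a one-sentence general description of a published scale. Past-month recall suits the screening cut-score, and the form used at each visit may be set in the full protocol; the content of Table 1 is not shown. That stands in part. It is not established that a past-month form will be handed out at days 7 and 14. But the article states one recall period and no other, and that period does not fit the endpoint. The daily online questionnaires on PTSD symptoms (Virtual follow-up sections) are not identified as the PCL-5 and do not change its recall period.

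Three stronger readings are tempting, and the documents do not support them.

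- *Most of every follow-up score describes time before treatment.* This is clear at day 7. At day 14 it is a bare majority with a 30-day month and exactly half with 28 days.
- *Both PTSD outcomes are compromised.* The article already describes a past-week use of the CAPS-5. That it does not name this as the endpoint version is an omission in a condensed article, not an error. A trial with the CAPS-5 tested at the same visits does not rest on the PCL-5 alone for a PTSD signal.
- *Power falls from about 78% to about 25% at day 14 and 10% at day 7.* These figures come from multiplying a standardised effect of 0.66 by 14/30 or 7/30 at 35 per arm. The 0.66 is the planning value for the ISI (Sample size {14}), and the SD is held fixed. Under the same equal weighting, the 16 shared days cancel, and the day-14 change equals 14/30 × (mean of days 0 to 13 minus mean of days −30 to −17). The SD of that part shrinks with the effect. How much of the standardised effect is lost depends on reporting error and on how symptoms vary from day to day, for which the article gives nothing.

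**Conclusion.** The point holds for the PCL-5. As written, its recall period does not match its use as a change score at days 7 and 14: about 75-77% of the recalled days at day 7 and 50-55% at day 14 precede the first dose, for a month of 28 to 31 days. The estimated mean treatment difference is therefore biased toward zero. This rests on two assumptions: that the stated recall period is the one used at follow-up, and that respondents give at least some weight to the earlier part of the month. Recency weighting would lessen the bias without removing it. The size of the loss, in points or in power, cannot be derived from the document.

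The reach is limited to one secondary outcome. It is worth correcting because that outcome is meant to supply an effect size and the correction is cheap.

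**What to change.** Keep the past-month PCL-5 for the screening cut-score above 30. Give the PCL-5 with past-week recall at days 0, 7 and 14, and define the outcome as change from the day-0 past-week score. State the recall period for each visit in the Self-assessments section. If a past-week form is already in use at days 0, 7 and 14, the only change needed is to correct that section.

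The cost is a minor amendment to the questionnaire instruction, and possibly one short extra questionnaire on day 0. The drawback is that the screening and baseline PCL-5 scores would no longer share a recall period, so they should not be compared or substituted for each other.

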#### Alcohol cue reactivity

This portion of the laboratory study consists of a presentation of a neutral cue (water) followed by an alcohol cue presentation and is used to assess alcohol craving. Immediately after each cue presentation, the participant will complete the Alcohol Urge Questionnaire (AUQ), Profile of Mood States (POMS), and Visual Analog Scale (VAS) based on the Alcohol Craving Questionnaire (ACQ).Neutral cue presentation: Individuals are instructed that they will be given a glass of water to handle for 3 min and that they may smell and handle the glass, but that they should not consume the water. In the presence of the research assistant, they are given the drink of water to hold and smell for 3 min. Following the presentation, the subject completes the assessments.Alcohol cue presentation: Individuals are instructed that they will be given their drink of choice to handle for 3 min and that they may smell and handle the drink, but that they should not consume the alcohol. In the presence of the research assistant, they are given their drink to hold and smell for 3 min. Following the presentation, the subject completes the assessments.

#### Clinical laboratory evaluations

Urine ethylglucuronide (EtG) testing: This assay is used to detect whether participants have consumed alcohol in the last 42 to 78 h.Urine drug/toxicology screen: A Clinical Laboratory Improvement Amendments (CLIA)-waived multidrug cup is an immunochromatographic assay for rapid, qualitative detection of drug combinations and their principal metabolites in urine at specified cut-off concentrations. A multidrug cup will be used to test several drugs.Fentanyl screen: This dipstick test strip assay is used for rapid, qualitative detection of at least 10 fentanyl analogs, including carfentanil, in urine.Urine pregnancy test: This assay is used to detect whether female participants are currently pregnant.Liver function test: This assay is used to detect alanine transaminase (ALT) and aspartate transaminase (AST), alkaline phosphatase (ALP), gamma-glutamyl transferase (GGT), serum bilirubin, total protein, and albumin. These tests will signify affected areas of the liver where damage may be occurring or occurred and help with diagnosis and treatment options.Serum blood test: This assay will provide a broad overlook of the health of a participant. The standard battery of tests includes CBC with differential, chemistry panel, and hepatic panel (transaminases, albumen, LDH, cholesterol, etc.).

